## Abstract

Background: Women with spinal cord injuries usually suffer from sexual dysfunction, such as alterations during arousal and an increase in the time to reach orgasm. However, little evidence has been found on its physiotherapeutic approach, as well as poor adherence to the latter. The aim of this study is to determine the effectiveness of two interventions to improve sexual dysfunction: the application of genital vibration and transcutaneous tibial nerve stimulation. Methods: This is a randomized clinical trial that will recruit 54 women who, one year after a spinal cord injury, suffer from sexual dysfunction associated with the latter. The participants will be randomized to three groups: (a) intervention group 1 treated with transcutaneous tibial nerve electrostimulation (*n* = 18), (b) intervention group 2 treated with genital vibration (*n* = 18), and (c) a control group (*n* = 18). The treatment time will be 12 weeks. Adherence to the treatment will be evaluated, as well as the effectiveness of the treatment, through the Female Sexual Function Index, the Sexual Quality of Life-Female questionnaire, quantitative sensory tests, and the improvement reported by the patient in terms of arousal and orgasm. The evaluations will be carried out before the treatment, at the end of the treatment and 3, 6 and 12 months after the end of the treatment.

## 1. Introduction

Neurological alterations after the Spinal cord injury (SCI) tend to produce changes in the sexual area. Four phases are differentiated in sexual function: arousal, plateau, orgasm and resolution [1]. The spinal cord suffers a nerve interruption that leads to different motor and sensory losses under the lesion level, which can generate a permanent disability [2]. About 80% of SCIs in Spain occur in the age range of 16–45 years [3]. Although SCI is less frequent in women (20%) [4], it is worth highlighting that, in the last years, the percentage of women with SCI has increased [5] and that 88% of these women experience sexual dysfunction (SD). This percentage, compared to the one found in the general female population (37%), is significantly higher [6], with its consequent impact at the personal and social level, and thus on the quality of life.

In addition to the motor and sensory deficits, the main autonomous alteration after SCI is autonomic dysreflexia, which occurs namely in injuries above T6 [7]. Autonomic dysreflexia can be related to some treatment and process of pelvic floor dysfunction.

Some women with SCI, once they are over the phase of spinal shock, can experience arousal through tactile stimuli directly applied on the genitals (reflective arousal), which remains unaltered if there is no affectation of the sacral spinal segments and peripheral sensitivity transmitters [8]. Both reflective and psychogenic arousal is observed in women with incomplete SCI [9]. At the peripheral level, sexual function can also be affected depending on the level and complexity of the SCI [10].

With respect to orgasm, the capacity to have it remains unaltered in women with intact sacral arch [11], although it has also been demonstrated that it can be induced through the vagus nerve [12]. In these cases, there is an increase in the time needed to reach an orgasm. Together with these physiological alterations, SD also tends to be associated with anxiety and depression in patients who present it, since sexuality is an essential part of their quality of life after the phase of spinal shock is over [13], and it is initially left aside in the rehabilitation process [8].

The literature shows improvements in SD in women through the application of genital vibration [14,15] or transcutaneous tibial nerve stimulation (TTNS) [16,17]. With respect to transcutaneous peripheral neuromodulation through the tibial nerve (L4—S3) [18], this presents an area of easy access to such nerve, which shares the same metameric area with the somatic and parasympathetic innervation of the pelvic floor (S2—S4) [19]. It is believed that the stimulation of its sensory afferent fibers blocks the abnormal afferences of this nervous region [20]. Therefore, through this neuromodulation, it is possible to regulate or modify the nerve activity on the different structures [21] and balance the excitatory and inhibitory impulses that produce improvements in vaginal arousal and lubrication [16].

Regarding vibrators, the literature shows two uses: (1) applied in bursts, after which there is an increase in blood flow associated with arousal; and (2) continuous vibration, which stimulates the high sympathetic explosion related to orgasm [22], also resulting in a better tissue perfusion, which can help to reduce muscle tone and increase relaxation [23].

It is important to propose treatment options for SD in women after SCI, since, currently, only educational programs are provided in most cases at late stages, and the patients refer an important deficit of information and treatment of SD [24]. Furthermore, due to the heterogeneity of levels and complexity of SCIs, this study will analyze the effect of two possible interventions plus a control group. None of these two propositions of intervention have presented any adverse effect [25,26].

We hypothesize that both types of stimulation, combined with educational programs, improve the evaluated sexual dysfunction symptoms measured through the Female Sexual Function Index (FSFI) and the Sexual Quality of Life-Female (SQOL-F) questionnaire. Particularly, the application of low-frequency genital vibration improves orgasm and TTNS improves arousal in women with SCI. The aim of the present study is to evaluate the effectiveness on FSFI and SQOL-F of an educational program plus TTNS and vibration in women with SD after SCI.

## 2. Materials and Methods

A protocol of a randomized clinical trial is presented with a blind randomization in the evaluation ([name]) and in the data analysis ([name]). The present protocol was registered in the platform https://register.clinicaltrials.gov/ (accessed on 16 November 2021) (NCT05122325). The study will be carried out according to guidelines and recommendations established for protocols by the SPIRIT statement [27].

The study is aimed at women with incomplete SCI, after which they had presented some type of SD. The candidates who participate in the study must meet the following inclusion criteria: women with American Spinal Injury Association or ASIA impairment B, C or D incomplete SCI (with preservation of the sacral arch and non-absent sensory evaluation of the lower dermatomes) below T6; aged 18–60 years without menopausal values of the follicle stimulating hormone (31–134 U/L) in a normal analysis; who present some type of SD secondary to SCI with at least 12 months of evolution; who live in Spain and are willing to go to the center of evaluations and treatments; and who sign the informed consent.

On the other hand, the study will exclude those women with active pregnancy and those who present pre-existing pathologies in the genital area, genital malformation, previous neurosurgery that affects the capacity of genital response, SD prior to the SCI, pressure ulcers, severe medical disease or any type of pathology in which the use of low frequency is contraindicated. In addition, the study will also exclude those with a psychiatric disorder or dependency on narcotics, and those who use selective serotonin reuptake inhibitors, antipsychotics or other drugs that affect the sexual response.

Regarding the sample size predicted for this study, 15 subjects were estimated for each group, with an effect size of 1.1, Df 28, α = 0.05, power (1 − β) = 0.80 (1 − β err prob) = 0.80u. Moreover, 20% more women will be recruited in order to consider the possible heterogeneity of the group and participants lost during the course of the study. Thus, a total of 54 women (18 women per group) will be recruited.

The project will be advertised in social networks, as well as in all the entities that belong to the ASPAYM (Association of people with spinal cord injury and other physical disabilities) in Spain.

The participants will be selected by non-probabilistic sampling from among those women who will reply to the advert and those associated with ASPAYM, who will be called for an interview in the University of Malaga or in the University of Castilla-La Mancha. The women who meet the inclusion criteria described above and sign the informed consent will be randomized by the Spanish version of the OxMar software [28] to either the control group (*n* = 18), the TTNS group (*n* = 18) or the vibration group (*n* = 18). Such distribution will be known to the lead researcher ([name]), who will oversee and indicate to each participant, in a closed envelope, the group they will be assigned to (Figure 1).

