### 2.4. Data Analysis

Firstly, a test will be performed to determine the efficacy of the randomization of the baseline characteristics of the participants in the 3 groups through the Shapiro-Wilk test and normal distribution diagrams.

Secondly, we will establish the rate of adherence of the different participants randomized to each of the groups and their percentage of abandonment, comparing their effect through the *t*-test or Mann-Whitney *U*-test to determine whether the groups differ in the demographic variables in V0.

Thirdly, the comparisons to determine the effect of the interventions on FSFI, SQOL-F and the quantitative sensory tests in different time points will be analyzed with ANOVA, or Kruskal-Wallis for non-parametric samples, using the Bonferroni method for the multiple comparisons between different evaluation time points. The results will be considered statistically significant if *p* < 0.05. Moreover, the differences between each evaluation after the intervention and the arousal and orgasm before the intervention will be recorded in binary variables of “improvement of arousal/orgasm”, with values 0 (same or lower arousal) and 1 (greater arousal). Thus, improvement in all variables will be compared with the rate of participants who increase their sensation in the three groups through the risk ratio and the χ^2^ test. The data analysis will be carried out using the SPSS software v.25.0 (IBM, New York, United States).

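### The stated 80% power is that of one uncorrected two-group t-test, not of the planned three-arm ANOVA or Kruskal-Wallis analysis with Bonferroni over visits

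*Protocol article*

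**What the plan says.** Section 2 (Materials and Methods) of the Protocol article gives the whole calculation in two sentences: "15 subjects were estimated for each group, with an effect size of 1.1, Df 28", with "α = 0.05, power (1 − β) = 0.80". It then adds an allowance, "20% more women will be recruited in order to consider the possible heterogeneity of the group and participants lost", and concludes that "a total of 54 women (18 women per group) will be recruited". The paragraph does not mention the third group, repeated visits or any correction for multiple tests.

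Other sections describe a different analysis:

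- Women are randomised to three groups of 18: tibial nerve stimulation, vibration and sham control (section 2).
- The Introduction states: "We hypothesize that both types of stimulation, combined with educational programs, improve the evaluated sexual dysfunction symptoms".
- Outcomes are measured at V0 and at four later visits, V1 to V4 (section 2.3).
- Effects on FSFI, SQOL-F and the sensory tests "will be analyzed with ANOVA, or Kruskal-Wallis for non-parametric samples", "using the Bonferroni method for the multiple comparisons between different evaluation time points", with significance at p < 0.05 (section 2.4). The number of comparisons is not given, and no correction across pairs of groups is stated.

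**The concern.** The degrees of freedom identify the test that was sized. A value of 28 with 15 per group can only be a comparison of two groups; a three-group one-way ANOVA with 15 per arm has 2 and 42. The protocol thus prints a power for one pairwise test at the full 0.05, while its analysis section uses a three-group test and spends some alpha on the visits.

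At stake is how the result will be read. If a comparison is not significant, readers will set it against the printed 80%. If the test actually used had 55% or 65% power for the same large effect, that inference would be too strong.

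**Working it through.** **Inputs.** From section 2: n = 15 evaluable and 18 recruited per arm, effect size 1.1, Df 28, α = 0.05, target power 0.80. From section 2.3: four post-treatment visits. Assumptions: 1.1 is a standardised mean difference d; tests are two-sided (sidedness is not stated); Bonferroni counts the four post-treatment visits.

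**Step 1: reproduce the plan's figure.** For a two-sample t-test, the noncentrality is δ = d√(n/2) and the power is P(|T| > t(1 − α/2; 2n − 2)), where T is noncentral t.

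- n = 14: power 79.99%, just short of the target.
- n = 15: δ = 1.1 × √7.5 = 3.01, df = 28, critical value 2.048, power 82.8%.

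So 15 is the smallest n that reaches 80%, and both n and Df match. A one-sided test would need only 11 per group, and reading 1.1 as Cohen's f for three groups would need only 4, so neither is what was done. The inflation also reproduces: 15 × 1.2 = 18, and 3 × 18 = 54.

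**Step 2: omnibus three-group ANOVA.** The noncentrality is λ = n Σ(μᵢ − μ̄)², with 2 and 3n − 3 df. At n = 15 the critical F is 3.22 at 0.05 and 4.87 at 0.05/4 = 0.0125.

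| Means in SD units | λ (n = 15) | α = 0.05 | α = 0.0125 |
|---|---|---|---|
| 0, 1.1, 1.1 (both arms work) | 15 × 0.807 = 12.1 | 86.1% | 69.2% |
| 0, 0, 1.1 (one arm works) | 12.1 | 86.1% | 69.2% |
| 0, 0.55, 1.1 (evenly spaced) | 15 × 0.605 = 9.08 | 74.2% | 52.9% |

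**Step 3: pairwise tests.** The formula is that of step 1 with a reduced alpha, at d = 1.1.

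| Alpha per test | Comparisons counted | n = 15 | n = 18 |
|---|---|---|---|
| 0.05 | one, as in the plan | 82.8% | 89.4% |
| 0.025 | two active-vs-control contrasts | 73.7% | 82.5% |
| 0.0125 | four visits | 63.5% | 74.2% |
| 0.00625 | two contrasts × four visits | 53.1% | 64.9% |

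Only the 0.0125 row uses a correction of the kind that section 2.4 states. The 0.025 and 0.00625 rows apply only if a correction across groups is added.

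**Step 4: what can be detected.** At α = 0.025 with 15 per arm, 80% power corresponds to d = 1.18.

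**Step 5: effect of adjusting for V0.** Adjustment raises the effective effect to d/√(1 − r²), where r is the correlation between V0 and V1. The documents give no r, so 0.5 and 0.6 are assumptions. The effective d is 1.1/√0.75 = 1.27 or 1.1/√0.64 = 1.375. With 15 per arm, power at α = 0.025 is about 86% or 91%; at α = 0.00625 it is about 70% or 78%.

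**The case against.** The strongest defence is that the planned test is an omnibus ANOVA and that section 2.4 attaches Bonferroni to evaluation time points, not to pairs of groups. If the group test is run once at 0.05 and both active arms reach d = 1.1, as the hypothesis suggests, power is 86%, above the target. This stands, and it rules out quoting one low range as the trial's power. Two limits remain. The same 86% arises if only one arm works, so an omnibus rejection does not show which arm does. Evenly spaced means bring it to 74%.

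A second defence is that three arms need not cost much alpha. Pooling the error over three arms (42 df) gives 75.2% at α = 0.025 with 15 per arm. In simulations with both arms at 1.1, Holm's procedure for two contrasts gave 79.5% per contrast, and an F-test followed by pairwise tests gave 80.1%. This also stands: a third arm alone does not push power far below 80%. The protocol names neither procedure, though, and neither deals with the visits.

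A third is that the 20% allowance covers the gap. With all 18 per arm evaluable, a pairwise test at 0.025 has 82.5%, but at 0.0125 it has 74.2%. The omnibus test at 0.0125 has 80.0% or 64.3%, depending on the means. The limitations paragraph in section 3 itself expects high abandonment, so full retention is not a safe basis.

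A reader might also infer that success requires both active arms to differ from control, for which joint power with 15 per arm is 73% at 0.05 and 60% at 0.025 (simulated). The Introduction hypothesises that both work, but nowhere makes this a condition of success. Finally, an article may leave the source of the 1.1 to the full protocol, so that is not counted against it.

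**Conclusion.** The point holds as a mismatch between the sample size and the analysis. The stated power is that of one uncorrected two-group t-test, and the calculation is correct for that test; it is not an arithmetic error.

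A reader might infer that the trial has some fixed power well below 80%, such as 53% to 74%. The documents do not support that, because they give neither the number of comparisons nor a correction across groups. What can be said is conditional on d = 1.1, 15 evaluable per arm and two-sided tests:

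- uncorrected omnibus ANOVA: 74% to 86%;
- omnibus ANOVA with Bonferroni over four visits: 53% to 69%;
- pairwise test: 63.5% with correction for four visits, 73.7% for two contrasts, 53.1% for both.

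Correction over visits, which the plan does state, is what clearly takes power below 80% if it is applied to the group comparisons with four visits counted. If Bonferroni was meant only for changes between visits, the uncorrected omnibus figures apply.

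**What to change.** Keep 54 women. In section 2, restate the power for the contrast, outcome, visit and alpha level that the analysis will use, and align section 2.4 with it. For example:

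*Each active-vs-control comparison of [named outcome] at [one named primary visit] is tested at two-sided α = 0.025. For d = 1.1 the power is 73.7% with 15 and 82.5% with 18 evaluable women per arm. With 15 per arm, the effect detectable with 80% power is d = 1.18.*

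If the group comparisons are instead to be tested at all four visits with Bonferroni, give the lower figures: 63.5% (15 per arm) or 74.2% (18 per arm) at 0.0125, and 53.1% or 64.9% at 0.00625 if the two contrasts are also corrected for. If the omnibus ANOVA is the primary test, give its power with the assumed pattern of means.

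Adjusting for the V0 value, which is already collected, would recover power. At α = 0.025 with 15 per arm it reaches 80% under the assumed correlations, but at 0.00625 it does not (about 70% and 78%). It should be offered as a gain conditional on those correlations, not as a guarantee.

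The cost is a rewritten paragraph, a decision on the primary comparison and probably a less favourable stated power. No extra patients, visits or measurements are needed.

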### 2.3. Data Collection

To preserve the confidentiality of the participants’ data, the researchers commit to complying with Organic Law 3/2018, of December 5th, on the protection of personal data and the Royal Decree that enforces it (RD 1720/2007). The participants will receive a code that will be related to the personal data only in a coding sheet. The evaluations will be conducted by a blinded researcher ([name]), who will initially collect the data of the participants in a data collection sheet: age, body mass index, data and type and level of spinal cord injury, pathologies or complications derived from the injury, allergies, pregnancies, type of deliveries and other diseases. Then, the participants trained by this researcher will complete the FSFI questionnaire, the SQOL-F, and the quantitative sensory test at the beginning of the treatment (V0, before the participants are randomized to any of the 3 groups), after the treatment (V1), and at 3 months (V2), 6 months (V3) and 12 months (V4) after the end of the treatment. [name] will be previously trained to standardize the measurements and will be blinded throughout the entire study to the randomization of the participants.

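### Allocation concealment is not assured: the lead researcher knows the allocation and hands it out, and nothing in the article separates that person from decisions on entry

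*Protocol article*

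**What the plan says.** The randomisation text is in section 2 (Materials and Methods) of the protocol article. The order of events starts well: "The women who meet the inclusion criteria described above and sign the informed consent will be randomized". The tool is named: women "will be randomized by the Spanish version of the OxMar software" to control, TTNS or vibration, 18 in each. The next sentence covers custody and delivery of the allocation: "Such distribution will be known to the lead researcher", "who will oversee and indicate to each participant, in a closed envelope, the group they will be assigned to".

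Two other statements bear on the point. Section 2.3 (Data Collection) places the baseline assessment V0 "before the participants are randomized to any of the 3 groups". It also gives the assessments to a separate person: "The evaluations will be conducted by a blinded researcher", who stays "blinded throughout the entire study to the randomization of the participants". The opening of section 2 describes both evaluation and data analysis as blind. The lead researcher is nowhere described as blind.

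**The concern.** Allocation concealment protects the decision to enrol. It requires that whoever judges eligibility, invites a woman or sets her date cannot foresee the group she would get. The article places knowledge of the allocation, oversight of the process and delivery of each assignment with one senior person, and states no barrier between that person and recruitment. A closed envelope conceals nothing from someone who already knows what is in it.

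Entry to this trial leaves room for judgement. Recruitment is non-probabilistic, with interviews at two universities, and some criteria are broad: any type of sexual dysfunction secondary to the injury, severe medical disease, other drugs affecting sexual response. Foreknowledge could lead, even without intent, to deferring or favouring women by expected response. With 18 per group a few such decisions move a mean noticeably, and a baseline comparison of that size has little power to reveal them. Blinding of the evaluator protects measurement and blinding of the analyst protects analysis. Neither acts at entry.

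**Working it through.** **1. The plan's own figure.** Inputs from section 2: effect size 1.1, df 28, α = 0.05, power 0.80, 20% added. Sidedness is not stated; two-sided is assumed because it reproduces the figure. A two-sample t-test with the noncentral t gives power 0.79994 at 14 per group and 0.828 at 15, so 15 per group, with df = 2 × 15 − 2 = 28. Then 15 × 1.20 = 18 and 18 × 3 = 54. The stated size is reproduced, and nothing below changes it.

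**2. What the text settles and what it leaves open.**

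| Question | Protocol article |
|---|---|
| Eligibility and consent before randomisation? | Yes (section 2) |
| V0 before randomisation? | Yes (section 2.3) |
| Who knows the allocation? | The lead researcher (section 2) |
| Who delivers it? | The same person, by envelope (section 2) |
| Known before or only after each enrolment? | Not stated |
| Who interviews, judges eligibility and schedules? | Not stated |
| Lead researcher barred from those tasks? | No such statement |
| Block size or other restriction? | None stated; 18/18/18 are given as group sizes |

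**3. How foreseeable assignments would be.** The expected number of correct guesses out of 54 depends on what the person deciding on entry knows. The block structures are assumptions. The figures for blocks of 54 and 6 come from simulating a guesser who knows all past assignments and the block totals and always names the group with most places left.

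| Knowledge of the person deciding on entry | Correct of 54 |
|---|---|
| Simple randomisation, no list: 54 × 1/3 | 18 (33%) |
| Past assignments known, one block of 54 with totals fixed at 18/18/18 | about 23 (43%), of which about 1.5 certain |
| Past assignments known, blocks of 6 | about 30 (56%) |
| Past assignments known, blocks of 3: 18 × (1/3 + 1/2 + 1) | 33 (61%) |
| Whole sequence held in advance | 54 (100%) |

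Access to the sequence matters far more than the equal group totals, which by themselves raise the figure only from 33% to about 43%.

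**4. What a bias would do (assumption, not in the documents).** Suppose foreknowledge brings women ν SD better into an active arm and women ν SD worse into control. The bias is 2ν. With no true effect, the two-sided t-test at 18 per group (df 34) has noncentrality 2ν × √(18/2) = 6ν.

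| ν (SD) | Bias 2ν (SD) | Share of 1.1 | Type I error |
|---|---|---|---|
| 0.05 | 0.1 | 9% | 6.0% |
| 0.10 | 0.2 | 18% | 9.0% |
| 0.25 | 0.5 | 45% | 30.8% |

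For scale: exchanging 2 of 18 women whose prognosis differs by 1 SD shifts each mean by 2/18 = 0.11 SD, a bias of 0.22 SD, or 0.22/1.1 = 20% of the planning effect. That is one chosen scenario inside the range above.

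**The case against.** A reader might infer that concealment is already broken. The documents do not support that. The sentence about the lead researcher follows the sentence that randomises women who are eligible and have consented, so it can be read as knowledge gained after each assignment, which is ordinary for a coordinator. No passage mentions a list drawn up in advance, and none says that the lead researcher interviews women or decides on entry.

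A reader might also infer that the plan randomises too early, or that the totals are forced to 18/18/18. Sections 2 and 2.3 already put eligibility, consent and V0 before randomisation. The group sizes are given without any method of restriction.

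Finally, a journal article may leave sequence generation, envelope preparation and enrolment roles to the full protocol, and silence on these is not a fault. The envelope may also serve to keep the group from others, such as the evaluator.

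All of this stands against the stronger reading. It does not remove the point, because the article does more than stay silent: it states that the allocation is known to the person who oversees the process and gives it out. The wording permits full foreknowledge, and no stated safeguard rules it out.

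**Conclusion.** The point holds as a weakness in the stated arrangement, not as a demonstrated failure. Allocation concealment is not assured. It would be lost only if the sequence is known in advance to someone who influences entry; then up to 54 of 54 assignments are foreseeable. If assignments are learned one at a time, correct guesses range from 18 to 33 of 54, depending on the restriction assumed and on whether past assignments are known to the person deciding on entry.

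No bias can be estimated from the documents. The type I error of about 6% to 31% rests entirely on the assumed bias of 0.1 to 0.5 SD and shows only what is at stake at 18 per group. The correction is worth making now because it is cheap and because selection at entry cannot be repaired after enrolment.

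**What to change.** Replace the sentence in section 2 on who knows and delivers the allocation with text to this effect:

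- The sequence is held in the randomisation software, or by an existing team member with no part in screening, enrolment or assessment.
- Each assignment is released singly to the treating physiotherapist, and only once eligibility, consent and V0 have been irrevocably recorded.
- The lead researcher and anyone else who decides on entry have no access to upcoming assignments.
- The treating physiotherapist, who will accumulate knowledge of past assignments, has no role in eligibility decisions.

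The article does not describe the software's release functions, so the rule is best written by role; if the software cannot restrict access, the independent holder does the same job. The cost is one changed passage, minor access-control work and some loss of convenience for the lead researcher. The order of V0 and randomisation and the sample size of 54 do not change.

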#### 2.1.2. Intervention Group 2: Genital Vibration

The women randomized to the genital vibration intervention group will be trained in the use of the Ferticare 2.0^®^Medical Vibrator (Multicept, Rungsted, Denmark) accepted by the Food and Drug Administration), and each participant will be provided with one of these devices. Initially, a practical session will be carried out with them, explaining to them that the frequency of use will be 70 Hz, with an amplitude of 1.5 mm. It will be recommended to them to gradually increase its use in time, with a limit of 30 min per day. The intensity will be increased progressively until small vibrations are found [15]. The vibrating head can be placed in any of the 5 genital points innervated by the pudendal nerve (clitoris, bilateral labia majora and bilateral perineum), using the minimum pressure required to maintain the position [25]. They will be asked to use it once per week, before or during a sexual encounter, and they will also be required to record its use and any doubt related to it. Every week, a 30-min visit will be performed to check how they are using it and solve any doubts that may emerge.

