#### 2.1.3. Control Group: Sham-Transcutaneous Tibial Nerve Stimulation

The guideline of application will be the same as that for the TTNS intervention group, but with the device switched off. The electrodes will be placed, and their location will be assessed to ensure that they are on the desired area. Once the intensity is lowered to reach the sensory threshold of the treatment, they will leave it at an intensity of 0. Then, the device in sham TTNS will be switch on for 30 s at the beginning, switch off for 20 min, and switch on for 30 s before stopping [30].

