## 4. Conclusions

This protocol will analyze, in a poorly studied field, interventions for sexual dysfunction in women after SCI to promote the social participation of the women included in this research. The randomized design will allow determining the specific field for improvement of each intervention in SD. The educational handout designed as a common guideline will benefit all the participants, regardless of the group to which they are assigned.

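### As written, the envelope tells each woman her group, which defeats the sham TTNS control for the outcomes she reports herself

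*Protocol article*

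**What the plan says.** **Allocation (section 2, Materials and Methods).** Eligible, consented women are randomized "to either the control group (*n* = 18), the TTNS group (*n* = 18) or the vibration group (*n* = 18"). The text continues: "Such distribution will be known to the lead researcher", "who will oversee and indicate to each participant, in a closed envelope, the group they will be assigned to".

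**Control (section 2.1.3).** The heading calls it sham TTNS: "The guideline of application will be the same as that for the TTNS intervention group, but with the device switched off". Electrodes are placed and checked, the intensity ends at 0, and the device is on for 30 s, off for 20 min and on again for 30 s.

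**Vibration (section 2.1.2).** Women are trained with an active vibrator, and "each participant will be provided with one of these devices". No sham vibrator is described.

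**Who is blinded.** Section 2 announces "a blind randomization in the evaluation" and in the data analysis. Section 2.3 has the evaluator "blinded throughout the entire study to the randomization of the participants". Participants are not named as blinded anywhere.

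**Outcomes (sections 2.2 and 2.3).** These are FSFI, SQOL-F, quantitative sensory tests, and reported improvement in arousal and orgasm. The women complete the questionnaires themselves.

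**The concern.** Placing electrodes, checking them and switching the device on briefly at both ends of a session make most sense if the woman is not meant to know that she gets no stimulation. The allocation sentence points the other way, because it has her told her group and one of the three groups is named control.

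The study's aim is effectiveness on FSFI and SQOL-F, and its arm-specific hypotheses concern arousal and orgasm. All of these depend on the woman's own report. A blinded evaluator cannot blind a questionnaire filled in by someone who knows her arm. If controls know they are controls, any difference in expectation is counted as treatment effect in TTNS versus control, the one contrast that the sham could have protected. A woman who has been told her group cannot later be made unaware of it.

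The vibration arm is recognisable whatever the envelope says. The two active treatments would thus be compared with control on unequal terms, while section 4 expects that "The randomized design will allow determining the specific field for improvement of each intervention in SD".

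**Working it through.** The point is about procedure, so the main check is to set the sections side by side.

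1. **What the envelope conveys.** Section 2 names three groups and has the assigned group indicated to each participant. Nothing says that active and sham TTNS share a label. Literal result: a control woman learns that she is a control.

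2. **What the sham needs.** Section 2.1.3 imitates TTNS and nothing else. It can separate stimulation from expectation only if women in the two TTNS arms cannot tell which they are in. Step 1 removes that condition.

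3. **What the stated blinding covers.** It covers the evaluator and the analyst (sections 2 and 2.3). FSFI, SQOL-F and reported arousal and orgasm come from the woman, so this blinding does not reach them. For the sensory test, section 2.2 establishes each participant's thresholds, and section 2.3 lists the test among what participants complete. If the threshold depends on her response, evaluator blinding protects it only in part.

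4. **Would a neutral label be enough?** Not by itself.
   - Active sessions last 30 min (section 2.1.1). The sham sequence adds up to 0.5 + 20 + 0.5 = 21 min, which is 30 − 21 = 9 min shorter if it is the whole session.
   - Section 2.1.3 also says that the sham follows the same application guideline as active TTNS, so the two statements in that section need reconciling.
   - Active TTNS runs at sensory threshold and the sham ends at 0, while eligibility requires some preserved sensation in the lower dermatomes. Women may feel the difference.

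5. **Vibration contrasts.** A woman who is given a vibrator knows that she is not in a TTNS arm. Vibration versus sham TTNS and vibration versus TTNS are open-label for participants.

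**The plan's own figure.** The sample size is not affected. A two-sided two-sample t-test with d = 1.1, α = 0.05 and power 0.80 gives n = 14.002, rounded up to 15 per group. Then df = 2 × 15 − 2 = 28 and power is 0.828. Adding 20%: 15 × 1.2 = 18 per group, and 3 × 18 = 54. The stated numbers reproduce.

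**Illustration only.** The document gives no size for reporting bias. Assume no true effect and a pure expectation shift of b SD. The two-group t-test then has noncentrality b × √(n/2).

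| Assumed b | Noncentrality, n = 15 | P(p < 0.05), n = 15 | Noncentrality, n = 18 | P(p < 0.05), n = 18 |
|---|---|---|---|---|
| 0 | 0 | 5% | 0 | 5% |
| 0.3 | 0.3 × √7.5 = 0.82 | 12% | 0.3 × √9 = 0.90 | 14% |
| 0.5 | 0.5 × √7.5 = 1.37 | 26% | 0.5 × √9 = 1.50 | 31% |

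The values of b are assumed. The planned analysis is a three-group ANOVA or Kruskal-Wallis test, not this t-test. The table shows direction and does not estimate the bias in this trial.

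**The case against.** The strongest reply is that the envelope's contents are unknown. A closed envelope is an ordinary concealment device, and the sentence may be loose wording in a condensed article. Figure 1, cited there, and any consent pages are not available to check. The envelope might carry a code or a neutral label. This stands as a limit: disclosure is the literal reading, not an established fact. But the text does not offer the milder reading, and one sentence would settle it.

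Several stronger inferences are tempting and are not supported:

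- *The protocol falsely claims participant blinding.* It claims none. A sham also equalises visits and contact, and section 2.1.3 states no purpose for it.
- *The missing vibration sham is an error.* It is an open design choice. The control heading names sham TTNS plainly, and nothing calls vibration versus control blinded. Only the interpretation needs a caveat.
- *The lead researcher sees the list before allocation.* The text says that this person will know the distribution, not that it is seen in advance. Section 2.3 already places V0 before randomization.
- *Relabelling makes TTNS versus sham a blinded contrast.* The timing and sensation differences could still reveal the arm, so blinding can be intended and checked but not asserted.
- *The false-positive rate is 12% to 26%.* That rests wholly on an assumed shift.

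**Conclusion.** The conflict is real and limited. Followed literally, the allocation sentence in section 2 defeats the sham control of section 2.1.3 for FSFI, SQOL-F and reported arousal and orgasm. It is a clash between two procedures and contradicts no blinding claim.

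The conclusion rests on two assumptions: that the envelope names the group as section 2 lists it, and that the sham is meant to keep women unaware of their arm. If the first fails because a shared label is already in use, only the wording needs correcting. The open-label status of the vibration contrasts holds under either reading.

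The document gives no basis for estimating the size of the bias. The point matters because the exposed outcomes are those named in the aim, and because disclosure cannot be undone.

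**What to change.** 1. In section 2, let the participant's envelope say only 'tibial stimulation' or 'vibration', so that active and sham TTNS share one label. Pass active or sham to the treating physiotherapist as a code.
2. State that TTNS versus sham TTNS is intended to be participant-blind. At V1, ask women in both TTNS arms to guess their group, and report the result.
3. Reconcile the 30 min active session (2.1.1) with the sham sequence of 20 min off between two 30 s periods (2.1.3), and with the statement in 2.1.3 that application is the same. Which timing is right is for the investigators to settle; the two must not reveal the arm.
4. State in sections 2.4 and 4 that vibration versus sham TTNS and vibration versus TTNS are open-label for participants, so these estimates include expectation.

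Cost: revised allocation wording and envelope text, one question at V1, and a more modest claim for vibration. No extra participants or staff are needed.
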